In the current study, we aim to increase the received dose of strengthening exercises aimed at the rotator cuff muscles in patients with long-lasting SIS without aggravating their symptoms and with minimal risk of adverse events. To achieve this, the intervention will start with exercises using low relative resistance but high volume (number of sets per session and frequency of sessions). This approach is also relevant, as resistance training with low intensity/resistance, high frequency and approximately 3–4 sets per muscle group is associated with the highest gains in muscle strength in untrained individuals [21]. All sets are to be continued to failure, as this maximises the gain in local muscle endurance [22]. Furthermore, the low resistance will minimise pain during exercises and protect the muscle from overload injuries, ensuring that all patients are able to complete the programme.

The focus of exercises is on isometric holds and slow dynamic strengthening with a long time under tension (TUT). A high TUT is achieved through exercises with a low contraction velocity and the inclusion of an isometric component to increase the exercise stimulus without increasing external resistance; this in turn reduces the peak load on the involved, and possibly damaged [16], muscles and tendons. Thus, exercises become safer and less painful, which again will allow patients to actually adhere to the exercise intervention. Furthermore, the isometric part will be performed with the shoulder in approximately 30–45 degrees of scaption, the position in which the compression forces on the supraspinatus muscle and tendon are lowest [23, 24]. Exercises will mainly focus on external rotation and abduction, functions in which both supraspinatus and infraspinatus muscles are highly active [25].

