### Interventions

Both groups will receive usual care consisting of an offer of referral to general rehabilitation in the municipal clinic under the Danish health Act § 140, sometimes with the option to instead choose a private physiotherapy clinic, partly at their own expense. The referral is standard procedure when a patient with SIS is considered to have a medically justified need for general rehabilitation, as identified during the examination at the orthopaedic outpatient department (secondary care unit). This procedure is based on the Danish National clinical guideline on diagnostics and treatment of patients with selected shoulder disorders [10], as exercise therapy is recommended as first line of treatment for SIS.

In the context of this study, usual care includes all treatment received by a patient during the time between baseline and follow-up, except that included in ‘Strengthen your Shoulder’. Therefore, usual care might include a range of treatment modalities including advice, stretching, exercises, manual therapy, massage, acupuncture and electrotherapy at the discretion of the treating physiotherapist and doctor. A description of usual care following the TIDieR guidelines [33] is included in Additional file 2.

Patients in the intervention group will, in addition to usual care, receive instructions regarding a home-based, progressive, high volume resistance-training programme immediately after randomisation. Instructions in the exercises are provided at baseline (week 0) and after 2, 5, 10 and 16 weeks. The exercise programme has been developed in cooperation with a team of experts with extensive knowledge of both exercise physiology and rehabilitation and training of patients with shoulder disorders (MC, TB, KT and MR). The design of the exercises, and their progression, is based on the relevant literature regarding exercise physiology, shoulder biomechanics and strength training principles for both healthy people and patients with shoulder disorders. A standard protocol for individual adaptation of the programme based on pain response is part of the intervention.

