A thorough description of the intervention, and modifications of the intervention, following the TIDieR guidelines [33], is included in Additional file 3, and the full set of strength training descriptors, as suggested by Toigo and Boutellier [35], are presented in Table 1. An online instruction video of the exercises will be made available upon publication of the main results of the trial, and a link to these is provided in Additional file 3.

**Table 1 Tab1:** Strength training descriptors [35] of the exercises performed in the intervention group

	Phase 1	Phase 2	Phase 3
Load magnitude	15–20 RM	10–15 RM	8–10 RM
Number of repetitions	To volitional muscular fatigue	To volitional muscular fatigue	To volitional muscular fatigue
Number of sets	3 sets	4 sets (2 per exercise)	6 sets (2 per exercise)
Rest in-between sets	60 s	60 s	60 s
Sessions per week	7 per week	3.5 per week	3.5 per week
Duration of experimental period	5 weeks	5 weeks	6 weeks
Contraction modes per rep			
Concentric	2 s	2 s	2 s
Isometric	5 s	5 s	5 s
Eccentric	2 s	2 s	2 s
Rest between reps	2 s	2 s	2 s
Time under tension	9 s	9 s	9 s
Volitional muscular fatigue	Yes	Yes	Yes
Rest between sessions	24 h	48 h	48 h
Anatomical definition of exercise	Yes	Yes	Yes
Range of movement	Exercise 1: 80° ER	Exercise 1: 80° ER Exercise 2: 45° ABD	Exercise 1: 80° ER Exercise 2: 45° ABD Exercise 3: 45° ER

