#### Interventions – adherence

Lack of adherence to an exercise intervention is a major problem when aiming at investigating the effect of an intervention. In the previously described studies that include unsupervised resistance training in rehabilitation of SIS patients, monitoring adherence is either done using a log-book filled in by the patients [9, 12] or not described at all [13]. Using only patient-reported measures of adherence may limit the possibility of detecting which exercise dose is actually received by the patient. Accordingly, in a recent systematic review, the authors did not identify a single measure of patient-reported adherence to unsupervised home-based rehabilitation exercises to be sufficiently investigated [36]. Furthermore, findings from one previous study revealed that the dose of exercises reported in exercise diaries were 2.3 times higher than that collected through a system which monitored the exact TUT, being the total time a muscle resists weight during each set [37]. This clearly underlines the relevance of collecting objective data on exercise adherence. In addition, it seems unlikely that patients are always able to ‘take’ precisely the exercise dose prescribed. This issue was unfolded in a recent study, revealing that, just 2 weeks after initial instructions, only 7 out of 29 young healthy individuals were able to use the correct TUT, when performing shoulder exercises with an elastic band [38].

In the SExSI-Trial, adherence to the add-on progressive high volume resistance training intervention will be captured using the BandCizer^©^. The BandCizer^©^ is a small device which is mounted on the elastic band during exercises to measure the TUT, number of repetitions and total work load for all exercises performed. Exactly TUT is a promising objective measure of exercise adherence, for which the BandCizer^©^ is specifically developed and validated [39–41]. By directly monitoring the actual TUT for the prescribed exercises a more precise and objective distinction between adherent and less adherent patients will be possible.

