#### Statistical methods – additional analyses

##### Subgroup analyses

For the outcomes SPADI score, abduction MVC and external rotation MVC, subgroup analyses investigating the modifying effect of scapula dysfunction, scapula dyskinesia, temporal summation of pain, conditioned pain modulation, pain pressure threshold (site 1) and pain catastrophizing, respectively, will be conducted. These will be performed using a cLMM, similar to the corresponding main analyses, but including a dichotomised value for the first measurement of the relevant variable as the interaction term and reporting the effect estimates for each subgroup.

The following sensitivity analyses will be performed for the primary outcome and reported together with the primary analyses in the primary trial report:A per protocol analysis, similar to the primary analysis, will be performed. From the IG, only patients who attended intervention appointments on weeks 0, 5 and 10 will be included in this analysis, while all patients in the CG will be included.Adjusted cLMM to adjust the effect of treatment allocation on SPADI score for any baseline differences between groups. Baseline variables will be included as covariates if (1) the difference between groups is more than 0.3 of the common SD for continuous outcomes, or (2) proportions are significantly different (*P* < 0.05) between groups, for binary outcomes.Sensitivity analyses to investigate the importance of the clinometric properties of the SPADI score may be relevant. This is based on a very recent study [58], which evaluates the SPADI score using the Rasch model. The study was published after initiation of this trial.

Three exploratory dose-response analyses will be performed. Only participants in the IG will be included in these analyses. First, the interacting effect of adherence to the intervention, TSP and CPM, on change in external rotation MVC, abduction MVC and SPADI score (outcomes), will be investigated. Secondly, whether the effect of TSP and CPM is mediated by adherence to the intervention will also be assessed. These analyses will be conducted as available-case analyses.

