For all included variables, data from each time-period (t_0_-t_1_, t_1_-t_2_ and t_2_-t_3_) will be included as repeated measurements in these analyses. The outcome variable is the change between first and last measurement in a time-period. ‘Adherence’ to the intervention is the total TUT in a time-period. ‘Central Pain Sensitization’ score (TSP or CPM) is the score from the last time-point in each time-period.

Additionally, results will also be presented for similar analyses adjusted for Usual Care, calculated for each time-period as the average of time spent on usual care, as reported by text-message, in all weeks included in the relevant time-period.

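### The adherence variable, total time under tension with sets run to failure, mixes compliance with shoulder capacity, so an adherence–strength association can appear without any training effect

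*Protocol article*

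**What the plan says.** The exposure is set in the dose-response text under Statistical methods – additional analyses: "Adherence’ to the intervention is the total TUT in a time-period". The outcome covers the same window: "The outcome variable is the change between first and last measurement in a time-period". The analysis concerns the effect of adherence, with two pain-sensitisation measures, "on change in external rotation MVC, abduction MVC and SPADI score (outcomes), will be investigated". A further analysis asks whether adherence mediates the effect of pain sensitisation.

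The Dose selection section says "All sets are to be continued to failure, as this maximises the gain in local muscle endurance". Table 1 gives the number of repetitions in all three phases as "To volitional muscular fatigue", at relative loads of 15–20, 10–15 and 8–10 RM. Its row "Time under tension" gives 9 s per repetition.

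Interventions – adherence says the device will "measure the TUT, number of repetitions and total work load for all exercises performed". The only adjustment stated for these analyses is self-reported time spent on usual care. They are labelled exploratory and use the intervention group only.

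**The concern.** If sets had a fixed repetition count, total TUT would mainly count exercise done as prescribed. With sets to failure, the repetitions in each set are themselves a performance test of the shoulder. A patient who becomes stronger or less painful during a period, for whatever reason, can do more repetitions on the same band and so accumulates more TUT without doing one more session. Exposure and outcome then share a cause. Because this happens within a phase, a term for period would not remove it.

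The dose-response relationship is a named secondary objective and has its own planned paper in the Dissemination policy. The mediation analysis uses the same variable, so repetitions cut short by pain would be read as low adherence.

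**Working it through.** **1. The plan's own figure.** Table 1: 2 s concentric + 5 s isometric + 2 s eccentric = 9 s per repetition. This reproduces.

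**2. TUT at full compliance (Table 1 only).** TUT = sessions per week × weeks × sets × repetitions × 9 s, with repetitions at the lower and upper end of the RM range.

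| Phase | Sessions | Sets | Lower end | Upper end | Ratio |
|---|---|---|---|---|---|
| 1 | 7 × 5 = 35 | 3 | 35×3×15×9 = 14,175 s | 35×3×20×9 = 18,900 s | 1.33 |
| 2 | 3.5 × 5 = 17.5 | 4 | 17.5×4×10×9 = 6,300 s | 17.5×4×15×9 = 9,450 s | 1.50 |
| 3 | 3.5 × 6 = 21 | 6 | 21×6×8×9 = 9,072 s | 21×6×10×9 = 11,340 s | 1.25 |

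Two fully compliant patients on the prescribed load can thus differ by 33%, 50% or 25%. A phase 1 patient at 20 RM can miss 1 − 15/20 = 25% of sessions and tie with a 15-RM patient who misses none (phase 2: 33%; phase 3: 20%). This spread shows misclassification of compliance. By itself it does not show a false dose-response.

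**3. How far a strength gain moves repetitions on an unchanged band.** Assumption, not in the documents: maximum = load × (1 + repetitions/30). From 17.5 repetitions with gain g, the new count is 30 × [(1 + 17.5/30)(1 + g) − 1].
- g = 4%: 19.4 (+11%)
- g = 9%: 21.8 (+24%)
- g = 15%: 24.6 (+41%)

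The 4% and 15% are the ends of the range of external rotation gains that the article reports from earlier trials; 9% is the gain it gives for the supervised-exercise trial.

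**4. Simulated null: strength changes, but not because of training.** One period of phase 1, 100 patients, correlation of exposure with strength change. Assumptions, none in the documents: the relation in step 3, half the gain acting on average over the period, strength change with mean 5% and SD 10–20%, about 70% of sets done with coefficient of variation 10–50%, measurement error 5%. Only positive significant results are counted, so nominal is 2.5%.

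| Scenario | Mean r | Significant positive |
|---|---|---|
| TUT, band unchanged | 0.25 to 0.86 | 73–100% |
| TUT, band re-set so repetitions stay within 15–20 | 0.16 to 0.62 | 36–100% |
| TUT, load fully re-set | about 0 | 2–3% |
| TUT, too-light band only, unrelated to gain | 0.00 | 2.7% |
| Sets completed | about 0 | 2–3% |

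A simpler model gives the same picture. It assumes session compliance of mean 73% and SD 17%, gain of mean 8% and SD 10–15%, 1–3% more repetitions per 1% gain, and 25–50% of the gain acting before the band is changed. Then r is 0.10–0.64, with two-sided false positives of 17–100% against a nominal 5%. With compliance of mean 60% and SD 30%, the weakest setting falls to about 6–9%.

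**5. Would capping TUT suffice?** Limiting each set to the upper prescribed repetition count in the simpler model still leaves roughly 13–99% false positives.

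**6. Are sessions immune?** The sets result in step 4 is nominal because compliance was simulated as unrelated to gain. If sessions correlate ±0.2 with gain (assumed), the Fisher transform gives atanh(0.2) × √97 = 0.203 × 9.85 = 2.00 against 1.96, so about half of trials are significant. With −0.2, the TUT correlation in the weakest setting turns negative (about −0.07 to −0.08).

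**The case against.** TUT is a reasoned choice. The article explains that diaries overstated dose 2.3-fold, that only 7 of 29 people kept the correct TUT, and that the device was developed and validated for TUT. The objective is a dose-response, and TUT does measure dose received. Counting sets discards information on how each set was performed. This stands, and is the reason to keep TUT in the analysis.

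Load is prescribed relative to capacity, and contact is repeated: "Instructions in the exercises are provided at baseline (week 0) and after 2, 5, 10 and 16 weeks". If the band follows strength closely, repetitions do not track it and the path closes. This also stands in principle. Details may be in Additional file 3, which is not shown. Keeping repetitions merely inside the prescribed range does not close the path (step 4).

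Sessions performed can respond to symptoms as well. The article itself lists the absence of early relief, and relief beyond a certain point, as barriers to continuing, and it suggests that pain sensitisation may alter adherence. Step 6 confirms that sessions are no unbiased substitute.

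The simulations use a one-period correlation for strength. The plan uses repeated periods with interaction and mediation, and nothing was calculated for SPADI.

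A reader might infer that patients with too light a band generate the dose-response. They do not: unless lightness is related to strength change it only adds noise. Combined with an unchanged band, in one setting it lowered r from 0.51 to 0.34.

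**Conclusion.** The point holds in a limited form. As defined, adherence combines compliance with capacity, and recovery from any cause can produce an adherence–strength association with no effect of training.

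The spread of 33%, 50% and 25% at full compliance follows from Table 1 alone. The false-positive rates rest on assumptions outside the documents and range from near nominal to 100%, depending on how often the band is re-set and how widely compliance varies. It would go too far to say that a spurious dose-response must appear, or that the net bias must be upward; the documents settle neither.

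The affected analyses are exploratory and confined to the intervention group. The primary comparison and the other between-group analyses do not use this variable. The point still merits a change, because the protocol itself fixes the definition and both a secondary objective and a planned paper depend on it.

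**What to change.** In the dose-response text under Statistical methods – additional analyses:

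- Pre-specify a compliance exposure for each period beside total TUT: device-recorded sets or sessions performed, divided by the number prescribed in Table 1 for that period.
- Run the dose-response and mediation analyses with both exposures.
- Label total TUT *dose received* rather than adherence.
- Draw a dose-response conclusion only if both exposures agree, and state that sessions performed may also respond to symptoms.
- Do not rely on a cap on TUT per set, which removes only part of the bias.

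The cost is one extra set of analyses and a few sentences of text. No new data are needed, provided sets or sessions can be read from the device record. The article states that the record holds TUT, repetitions and work load but does not mention sets or sessions, so this should be confirmed first.

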### Possible effect modifiers

Patients with long-lasting SIS have lower mechanical pressure pain thresholds (PPT), both at the shoulder region and in other anatomical regions (such as the tibialis anterior), which may reflect an increased manifestation of peripheral and central pain sensitisation [26]. Pain sensitisation modulates the patients’ pain experience and, furthermore, the presence of hyperalgesia or referred pain before decompression surgery significantly worsens the outcome after 3 months [26], while more pain catastrophizing is related to persistence of symptoms in patients with long-lasting SIS [27]. It therefore seems likely that manifestations of peripheral and central pain sensitisation, and peripheral adaptations to long-lasting pain, could also affect the outcome of an exercise intervention. This could be either through an alteration in adherence to the intervention due to pain sensitisation, or through other mechanisms related to central pain sensitisation and peripheral adaptations.

The effect of scapula function on treatment outcome in patients with SIS is often debated, and one could argue that the increased emphasis on rotator cuff muscles, as is proposed in the current trial, would neglect an important aspect of the rehabilitation. Accordingly, it has been suggested that rotator cuff emphasis should only be after scapula control is achieved, as insufficient dynamic stability of the scapula could cause abnormal shoulder kinematics and impingement symptoms [28]. Assuming this, the effect of the add-on intervention in the current study, focusing mainly on strengthening exercises for the rotator cuff, could be modified be the presence of scapula dyskinesis. However, Mulligan et al. [29] recently found that treatment outcome was not significantly different between patients randomised to scapula stabilisation first, or rotator cuff strengthening first, questioning the importance of maintaining a scapula focus in the beginning of rehabilitation.

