#### Secondary objectives

To investigate the effectiveness of adding a 16-week simple home-based shoulder strengthening exercise programme to usual care, compared to usual care alone, on changes in shoulder abduction and external rotation strength from baseline to end of treatment (16 weeks) in patients with SIS.To investigate the modifying effects of pain sensitisation, pain catastrophizing and scapula function on the effectiveness of adding a 16-week simple home-based shoulder strengthening exercise programme to usual care, compared to usual care alone, on changes in patient-reported shoulder function and shoulder abduction and external rotation strength from baseline to end of treatment (16 weeks) in patients with SIS.To investigate the dose-response relationship between objectively monitored adherence to the add-on intervention and change in patient-reported shoulder function, shoulder abduction strength and external rotation strength.To investigate the relationship between central and peripheral pain sensitisation and change in patient-reported shoulder function, shoulder abduction strength and external rotation strength, and to what degree this is mediated through adherence to the intervention.

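### In the mediation analysis, sensitisation (TSP/CPM) is read at the end of each period, after the adherence it is supposed to influence; this can produce false mediation or dilute a true effect

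*Protocol article*

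**What the plan says.** The last secondary objective is to study how sensitisation relates to change in shoulder function and strength, and "to what degree this is mediated through adherence to the intervention". The dose-response part of the section *Statistical methods – additional analyses* repeats the question: "whether the effect of TSP and CPM is mediated by adherence to the intervention will also be assessed". The background section *Possible effect modifiers* gives the reasoning, namely that sensitisation may act through "an alteration in adherence to the intervention due to pain sensitisation". In all three places sensitisation is the exposure and adherence the mediator.

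The variables are then defined for each of the periods t0–t1, t1–t2 and t2–t3 (weeks 0–5, 5–10 and 10–16):

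- Adherence "to the intervention is the total TUT in a time-period".
- "The outcome variable is the change between first and last measurement in a time-period".
- The sensitisation "score (TSP or CPM) is the score from the last time-point in each time-period".

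"Only participants in the IG will be included in these analyses", and the analyses are labelled exploratory and run on available cases.

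Two other places bear on this. Table 2 lists TSP and CPM among the secondary outcomes that the intervention is expected to improve, and labels them t1 to t3. In the section *Dissemination policy*, the working title of the paper on pain sensitisation makes sensitisation the mediator of the adherence dose-response, which is the reverse direction.

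**The concern.** A cause has to come before its effect. For the period from week 5 to week 10, the plan asks whether the week-10 sensitisation score influenced how much the patient exercised between weeks 5 and 10. It cannot have done so. An association between the two could arise because an earlier level of sensitisation persisted, or because exercise or symptom change altered sensitisation. The model cannot tell these apart, and it attributes all of the association to the path from sensitisation to adherence.

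The protocol's own hypothesis makes the reverse path plausible, since Table 2 expects the intervention to improve TSP and CPM. The same end-of-period score also enters the adherence-by-sensitisation interaction, where it may partly be a consequence of the outcome being modelled. The effect-modification subgroup analyses, by contrast, use the first measurement of each variable. What is at stake is one stated secondary objective and one planned paper.

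**Working it through.** **Time order, from the text**

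| Role in the stated question | Variable | When it is fixed |
|---|---|---|
| Exposure | TSP or CPM | last visit of the period |
| Mediator | total TUT | accrues across the whole period |
| Outcome | change in SPADI or MVC | first to last visit of the period |

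The exposure is read after the mediator is complete and at the same visit as the outcome's end value. No lag or justification is given.

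**Size of the consequence**

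The protocol gives no figure to reproduce here. The inputs from the document are 100 patients in the intervention group (section *Sample size*), three periods and a two-sided 5% level. Every path size below is an assumption, in SD units, with higher sensitisation meaning worse.

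- TUT_t = a·S_(t−1) + u + error, where u is a stable personal tendency giving a within-person TUT correlation of 0.3
- Y_t = 0.3·TUT_t + error
- S_t = 0.6·S_(t−1) + c·TUT_t + error, with error variance 1 − 0.6² = 0.64

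The analysis regresses TUT on S (path a), then Y on S and TUT (path b), with cluster-robust standard errors. Mediation is declared if both paths are significant. The indirect effect is a × b.

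*Hand check, false effect.* Set a = 0 and c = −0.3. In the first period Cov(TUT, S_end) = −0.3 and Var(S_end) = 0.36 + 0.09 + 0.64 = 1.09. The apparent path a is −0.3/1.09 = −0.275, and the apparent indirect effect is −0.275 × 0.3 = −0.083, although the truth is 0. The simulation over three periods gives −0.090.

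*Hand check, dilution.* Set a = −0.2 and c = 0. The true indirect effect is −0.2 × 0.3 = −0.060. With the end score, Cov(TUT, S_end) = 0.6 × (−0.2) = −0.12 and Var(S_end) = 1, so the estimate is −0.12 × 0.3 = −0.036. That is a loss of 40%, which is one minus the assumed autocorrelation of 0.6. The simulation also gives −0.036.

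*Rate of declared mediation when sensitisation has no effect on adherence:*

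| Path c, adherence → later sensitisation | End score, as planned | Start score, three periods |
|---|---|---|
| 0 | 5–6% | 6% |
| −0.1 | 39–47% | 8% |
| −0.2 | 91–93% | 14% |
| −0.3 | 99–99.8% | 20% |

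The ranges in the middle column are across repeated simulations. If only the symptom change lowers the end score (path −0.3), the rates are 34% with the end score and 7% with the start score. If adherence raises the score by 0.1 or 0.2, a true indirect effect of −0.060 is estimated as −0.001 or +0.035, so it is cancelled or changes sign.

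**Is the start-of-period score enough?**

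Not by itself. The t1 score already carries the effect of exercise in t0–t1, and patients who exercised more then tend to exercise more later. Using only t1–t2 and t2–t3, for c from −0.1 to −0.3, the start score still gives 10–32% false mediation at a TUT correlation of 0.3 and 17–78% at 0.6. Adding TUT from earlier periods as a covariate brings the rate back to about 5%.

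**The case against.** Four things can be said for the plan.

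1. *False mediation is conditional.* It needs a path from adherence or symptom change to the end score, and without one the error rate is nominal. This stands. A reader might infer that the analysis is bound to give false mediation, or that a rate near 100% is the expected one. The documents do not support that: Table 2 makes a reverse path plausible but gives it no size, so only the range can be stated. Even at zero path, though, the end score estimates a diluted effect.

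2. *The definition may have been written for the reverse question.* The planned paper's title makes adherence the exposure and sensitisation the mediator, and an end-of-period score suits that order better. This stands as a reason to settle the direction first. It does not rescue the analysis for the question asked in the section *Secondary objectives* and in the analysis section.

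3. *The end score may be the only one available in t0–t1.* Table 2's t1–t3 label suggests that TSP and CPM were first measured at week 5; Fig. 1, which would settle this, is not shown. That may explain the rule for one period, but not for the other two.

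4. *The analysis is exploratory and confined to the intervention group.* This stands and limits the severity. A reader might infer that the trial's main findings are at risk. They are not: the primary outcome, the randomised comparison, the sample size and the effect-modification subgroup analyses do not use this definition.

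**Conclusion.** The point holds at moderate severity. The protocol fixes a rule that does not answer the question it poses; this is not a detail left to the analysis plan. The reversed time order follows from the text alone.

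The size of the harm rests on assumed paths: adherence to outcome 0.3, sensitisation autocorrelation 0.6 and TUT correlation 0.3. On these, false mediation runs from about 5–6% with no reverse path to 99% or more at −0.3, and a true indirect effect with no reverse path shrinks by about 40%. The defensible statement is that the analysis can mislead in either direction, not that it will. A reader might also infer that moving to the start-of-period score repairs everything; the remaining 10–78% shows that it does not unless earlier adherence is also handled. The effect on the interaction analysis follows from the same time order but was not quantified.

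**What to change.** 1. State which variable is the mediator. Reconcile the section *Secondary objectives* and the additional-analyses section with the paper title in the section *Dissemination policy*. If both directions are wanted, define them as two analyses, each with its own timing.
2. For sensitisation → adherence → outcome, take TSP/CPM from the first time-point of each period: t1 for t1–t2 and t2 for t2–t3. Include t0–t1 only if a t0 score exists.
3. Adjust both regressions for TUT in the earlier periods.
4. Use the start-of-period score in the adherence-by-sensitisation interaction as well, in line with the first measurement used in the subgroup analyses.

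The cost is small: changed definitions and one added covariate set, using data already collected. One of the three periods may be lost if TSP/CPM were first measured at t1, and the adjustment costs some precision. Because adjusting for earlier TUT can itself weaken a true effect when unmeasured traits drive adherence, report the unadjusted estimate beside it.
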